**Figure 2 figure2:**
[figure not shown]
Map of the study site [32].

### Assignment of Treatments

We randomly allocated the 36 clusters in an equal ratio to intervention or control groups but with stratification by socioeconomic status of the clusters. We generated the random allocation sequence using SAS software (SAS Institute).

### Recruitment, Inclusion and Exclusion Criteria, and Consent of Mothers and Their Families

We visited the pregnant women identified in the census, and recruited eligible women in their third trimester of pregnancy into the trial. We updated the census data, including the pregnancy screening, every 3 months to identify and recruit potentially eligible women once they reached their third trimester. We included pregnant women who were 16 to 40 years of age and who had no more than 3 living children. We excluded women who planned to migrate from the Mirpur area after delivery and women with medical records of heart disease, tuberculosis, gestational diabetes, or eclampsia in previous pregnancies, from the trial. In addition, we excluded mother-infant pairs where the child had congenital abnormalities, had a very low birth weight below 1.5 kg, or were admitted to a neonatal intensive care unit. We used the same approach to recruitment in both intervention and control clusters. Trained project staff obtained written informed consent from the eligible women and their husbands. Based on experience with similar projects in Bangladesh [33,34], we expected at least 95% of the mothers would consent to participate. We anticipated excluding up to 30% of the women mainly related to their desire to migrate back to their home village after the delivery [34].

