### Statistical Analyses

Data analysis will be by intention to treat. Analyses will be conducted at the mother-infant dyad level but will be adjusted for the community-cluster randomization [55]. The primary analyses will compare the prevalence of stunting (length-for-age < –2 *z* score) in children at 18 months of age using Pearson chi-square tests and 95% CIs for the group difference, with adjustments for clustering. We will report the results for 2-sided 5% tests.

Secondary analyses will examine each outcome variable (length-for-age, percentage EBF, duration of breastfeeding, percentage doing bottle feeding, percentage giving complementary feeds, percentage receiving diverse food groups, and mean nutrient intakes), taking account of the repeated measurements within children by using separate mixed models. We will use linear mixed models for the continuous outcomes (eg, height for age *z* score, duration of breastfeeding, Ages and Stages Questionnaire, Bayley, and Wechsler scales) and generalized linear mixed models for noncontinuous outcomes (eg, logistic mixed models for binary outcomes, such as percentage stunted or percentage exclusively breastfeeding). Models will include the treatment group as a fixed effect and infants as a random effect to account for the repeated measurements, and community cluster as a random effect to account for the cluster effect. The models will evaluate the impact of the interventions over time by testing for an interaction between time and the intervention group.

We will conduct analyses to identify the baseline characteristics of the mother-infant dyads who may benefit most from the intervention. Model assumptions will be checked, and appropriate adjustments to the analysis will be made where necessary. We will use Stata software (Stata Corp) for all analyses, with the “mixed” command to fit linear mixed models, the “melogit” command to fit mixed-effects models for binary outcomes, and the “mepoisson” command to fit mixed-effects models for event count data.

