## Results

Using satellite maps, we digitized all structures in the study areas, and from a brief census of all mapped residences, we identified a population of 65,535 people. We created a population database linked to the map structure and applied this information to define 36 clusters with 500-meter buffer zones. We randomly allocated the 36 clusters in an equal ratio to intervention or control groups but stratified by the socioeconomic status of the clusters. We screened for pregnant women in all residences and identified 5377 eligible pregnant women.

From July 2011 to May 2013, we carried out a baseline survey. In the third trimester, we examined 2050 pregnant women, including 1056 women in the intervention group and 994 women in the control group. The women participating in the trial had 1883 birth outcomes, with 993 in the intervention group and 890 in the control group. The study followed up the women who delivered the infants until 18 months of life. In December 2012, we began assessing the original cohort and completed 18 months of study follow-up in October 2014 for participants. Among them, 692 in the intervention group and 551 in the control group remained in the study until 18 months follow-up, with 301dropouts in the intervention and 339 dropouts in the control group. We continued evaluating the cohort until the children were 36 months of age, with child growth and development outcomes measured at 24 and 36 months. The long-term follow-up began in January 2015 and ended in February 2017. We have now completed the data cleaning and processing and have started analyses of the data.

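### Women were recruited one by one after the clusters had been allocated, but the primary stunting comparison adjusts for clustering only and names neither enrolment covariates nor the SES stratum.

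*Protocol article*

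**What the plan says.** - **Allocation.** The section on assignment of treatments allocates 36 clusters in equal numbers, stratified by cluster socioeconomic status. It gives no date and says nothing on who knew the result. The Results tell of the allocation before the baseline survey.
- **Recruitment.** The team "updated the census data, including the pregnancy screening, every 3 months to identify and recruit potentially eligible women" once they reached the third trimester, and took individual written consent. One exclusion rests on stated intention: "We excluded women who planned to migrate from the Mirpur area after delivery". The same section says recruitment was done the same way in both arms.
- **Timing and numbers.** "From July 2011 to May 2013, we carried out a baseline survey". The Results also state: "We screened for pregnant women in all residences and identified 5377 eligible pregnant women". Of the women entered, "we examined 2050 pregnant women, including 1056 women in the intervention group and 994 women in the control group".
- **Primary analysis.** Under Statistical Analyses, stunting at 18 months is compared "using Pearson chi-square tests and 95% CIs for the group difference, with adjustments for clustering". No enrolment covariate and no SES stratum is named, either there or for the secondary mixed models.
- **Data available.** The sections on socioeconomic status, household food security and schedule of data collection show that education, occupation, assets, food security and maternal characteristics were recorded at enrolment.

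**The concern.** Randomising clusters balances clusters, in expectation. It does not balance the women who enter once a cluster's arm is fixed. Here each intervention cluster had a local peer counselor and the intervention was a home-visit programme. One entry criterion was whether the woman said she would stay, and an offer of support at home could change that answer. Following the same procedure in both arms does not guarantee the same responses to it.

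If the women who entered differ between arms in, say, education or household assets, the difference in stunting carries that case mix along with any counselling effect, in either direction. The clustering correction widens the interval but leaves the point estimate where it is. Intention to treat keeps enrolled women in their allocated arm, but has no bearing on who enrolled. The variables that could correct the measured part of such a difference were collected, and the primary analysis does not use them.

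**Working it through.** **1. Inputs from the article.** 36 clusters; 692 and 551 children retained at 18 months (1243 in all); ICC 0.015; two-sided 5% test; planned stunting 35% against 25%, so 30% on average.

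The plan's sample size reproduces with these values. 460 per arm (90% power, continuity-corrected) × (1 + 38 × 0.015) = 722.2. Dividing by 0.78 for loss and 0.95 for participation gives 974.6, the stated 975 per arm. The ICC and test level used below are therefore the plan's own.

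**2. Length of enrolment after allocation.** July to December 2011 (6) + 2012 (12) + January to May 2013 (5) = 23 calendar months.

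**3. Overall entry.** 2050/5377 = 38.1%. The plan's expectations (95% consent, up to 30% excluded) would give 0.95 × 0.70 = 66.5%, or 3576 women. The denominator is unclear and is not split by arm, so this figure is context only.

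**4. Precision of the primary comparison.**
- Average cluster size: 1243/36 = 34.5.
- Design effect: 1 + 33.5 × 0.015 = 1.50.
- With equal arms of 621.5 and 30% stunting: SE = √(2 × 0.3 × 0.7/621.5 × 1.50) = 0.0319, about 3.2 points.
- With the actual arms and 35% stunting: SE = √(0.35 × 0.65 × (1/551 + 1/692) × 1.503) = 0.0334, about 3.3 points.

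**5. Illustration, under assumed inputs.** Bias = (arm difference in the share with a trait) × (difference in stunting with and without it). The article gives neither factor.
- Assume a 10-point imbalance in low maternal education and a 20-point stunting gradient: 0.10 × 0.20 = 2.0 points.
- Rejection rate under no true effect = Φ(b/SE − 1.96) + Φ(−b/SE − 1.96). For b = 2.0 points this is 9.6% with SE 0.0319 and 9.2% with SE 0.0334.
- Imbalance of 5 to 15 points and gradient of 10 to 25 points: bias 0.5 to 3.75 points, type I error 5.3% to 21.8% (SE 0.0319).

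These rates restate the assumed imbalance and gradient on the scale of the test. They do not estimate what happened in this trial.

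**The case against.** The strongest case on the other side is that nothing in the article shows an arm difference in who entered. Recruitment was the same in both arms, allocation was stratified by cluster SES, and the counts are close (1056 against 994; z = 62/√2050 = 1.37 against an even split, ignoring clustering). A cluster-adjusted comparison without covariates is a legitimate primary analysis, and an unseen analysis plan may name adjusted analyses. Regression also cannot remove selection on motivation or intention to stay.

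Most of this stands as a limit on the claim. It does not remove the point. Similar counts do not show similar case mix, stratifying clusters does not control who enters within them, and the article itself fixes the primary test.

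A reader might infer more than the text supports:
- **That the test is wholly unadjusted.** It is adjusted for clustering.
- **That allocation was known to recruiters and women.** The article is silent on this. It is an inference from the intervention and the order of the narrative.
- **That 38% entry shows selection, or refutes the statement that "we expected at least 95% of the mothers would consent to participate".** The 5377 came from screening all residences. It may include buffer-zone residents, women who planned to migrate, or women never approached. Recruitment also had a target of 1950 dyads and counselor capacity for about 1000 intervention women. The figure is not a consent rate and says nothing about differences between arms. The consent expectation can stand as an expectation.
- **That unequal retention (692/993 = 69.7% against 551/890 = 61.9%) shows unequal enrolment.** It concerns what happened after entry.
- **That comparing women found in the first census with later ones would settle the matter.** Women from the first census were still recruited in the third trimester, so their consent too may have followed allocation.

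**Conclusion.** The point holds in a limited form. Individual recruitment over 23 months followed cluster allocation, with no masking of recruitment described and one exclusion resting on the woman's own stated plan. The primary analysis cannot correct measured case-mix differences that may have arisen, and it does not name the stratum used in randomisation. The order of events rests on the sequence given in the Results, since the randomisation is undated.

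The actual size is unknown. Under the assumed 2-point bias, the type I error would be about 9-10% instead of 5%. The wider assumed range runs from almost no effect (5.3%) to about 22%. The documents do not show that any such bias occurred. The change is worth making because it is a better primary analysis at almost no cost.

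**What to change.** In Statistical Analyses, make the primary 18-month stunting comparison a cluster-adjusted regression that includes:
- the SES stratum used in randomisation;
- a short list of enrolment covariates, for example maternal age, education, number of living children, household asset score and food security.

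Report a standardised risk difference with its 95% CI, and keep the cluster-adjusted chi-square as a supportive analysis. Fix and date the covariate list before the arms are compared. The Results say analyses have started, so the text should also state what had been looked at by that date.

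The cost is plan wording and one further model on data already collected. The downside is modest model dependence, which with 36 clusters is a reason to keep the list short. The text should also say that the adjustment deals with measured differences only, and not with selection on motivation or intention to stay.

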### Intervention Plan

We selected the trial intervention due to its feasibility, previous testing in urban populations in Dhaka [34], and likely future sustainability. We expect the proposed individual peer counseling education will have sufficient intensity to alter infant and young child feeding practices and improve young children's growth. After 1 year of preparation for the trial, we delivered the interventions to recruited pregnant women until their children reached 1 year of age.

This approach promoted appropriate infant and young child feeding through a program of home-based peer counseling by trained local women from the mothers' community. The peer counselors reached mothers who delivered at home and allowed the messages to reach other key family members who played a role in supporting breastfeeding and influenced the choice of foods for the infant. The main messages encouraged early initiation of breastfeeding, promoting EBF during the first 6 months of life, promoting appropriate timing of the introduction of complementary feeds, and ensuring an adequate frequency of feeds and diversity of foods used in their preparation.

#### Selection and Training of Peer Counselors

Women with personal breastfeeding experience and at least 6 years of schooling who resided in the same area and who were motivated to work to become peer counselors were selected. We trained the peer counselors using the joint WHO/UNICEF (United Nations International Children's Emergency Fund) breastfeeding counseling course adapted to the local language and culture and validated in a previous study [34]. They were trained for 40 hours (4 hours daily for 10 days). Counseling skills were taught mainly by demonstrations and role-play. The topics included listening to mothers, learning about their difficulties, assessing the position and attachment of infants during breastfeeding, building mother's confidence, giving support, and providing relevant information and practical help when required. During the course, the trainee counselors practiced antenatal and postpartum counseling at the field site with pregnant women, mothers with newborns, and infants aged 1-12 months. We trained counselors in how to use locally available foods for complementary feeding of infants and young children and how best to demonstrate these food preparation skills to mothers.

We anticipated that each peer counselor would support up to approximately 50-60 mothers and thus provide support to about 1000 women receiving the intervention. We recruited and trained 18 peer counselors (one in each cluster). Senior infant feeding counselors monitored the performance of the peer counselors at least 4 times during the study.

#### Counseling Schedules

We scheduled 13 visits by the peer counselors: 2 before delivery, 4 during the first month, 5 monthly visits from age 2 to 6 months, and 3 monthly visits at age 9 and 12 months. The counselors were free to make additional visits if the mother's circumstances required them. The counseling took place at home to include key family members (eg, mother-in-law and fathers) in the counseling sessions. The duration of each visit was from 20 to 40 minutes.

#### Antenatal Visits

During the 2 antenatal visits, peer counselors prepared and informed the mothers and other family members who supported the mothers at delivery about the importance of holding the infant within a few minutes of delivery and breastfeeding initiation within 1 hour of delivery. They discouraged prelacteal feeds and encouraged the mothers to eat more foods and rest during the third trimester. These meetings also covered problems with breastfeeding that the mothers might have encountered and provided strategies to deal with them.

#### Visits in the First Month of Life

The mothers were contacted 4 times by the peer counselors (within 48 hours of delivery, at 5-7 days, at 10-14 days, and at 24-28 days). During these visits, EBF was encouraged, and any barriers to EBF, such as sore nipples, problems with attachment and position of the baby during feeds, family pressure to introduce other foods, and mothers' doubts about the adequacy of their breastmilk, were resolved. If the counselor could not resolve these issues, the mothers were referred to the senior infant-feeding counselors.

#### Visits From 2 to 6 Months of Life

The mothers were contacted monthly by the peer counselors, who addressed any specific problems and continued to provide support for EBF, especially how to deal with family pressures, the introduction of other foods, and concerns about the adequacy of the infants’ growth. From 5 months of age, specific messages covered the importance of complementary feeding and demonstrations and preparation of complementary foods from homemade, regular family food. Mothers were given measuring bowls (250 ml) and spoons to promote the age-specific frequency of complementary feeding. According to the UNICEF guidelines, mothers received hands-on training on the frequency and amount of complementary feeding [35]. For the average healthy breastfed infant, meals of complementary food are needed 2-3 times (half a bowl of 250 ml) per day at 6-8 months of age and 3-4 times per day at 9-11 months and 12-23 months of age with additional nutritious snacks. Mothers were discouraged from using bottles for complementary feeding.

#### Visits From 6 to 12 Months of Life

The mothers were contacted twice at 3-month intervals by the peer counselors. They were encouraged to continue breastfeeding and supported to give an adequate frequency of complementary feeds and appropriate diversity of foods. There were further demonstrations on the preparation of complementary feeds as needed.

#### Management of Interventions

We recruited 3 breastfeeding counselors who trained the peer counselors under the supervision of 1 of the investigators (RH) and the research investigator (GA). The breastfeeding counselor provided technical support to the peer counselors and helped them resolve problems encountered during the implementation of the trial interventions by regular meetings with them in the field. The research officer supervised, monitored, and provided the necessary support for troubleshooting for breastfeeding complementary feeding. To facilitate the overall implementation process, we established an advisory committee consisting of local health officers, local government officials, representatives of mothers' groups from the community, representatives of the Bangladesh Breastfeeding Foundation, other relevant nongovernmental organizations, and project staff.

### Evaluation Plan

We applied a range of quantitative data collection methods to assess the primary and secondary outcomes, including pretested structured questionnaires and anthropometric measurements. Figure 3 presents a timeline depicting the schedule of data collection.

**Figure 3 figure3:**
[figure not shown]
Schedule of enrollment, interventions, and assessments. IYCF: Infant and Young Child Feeding.

### Primary Outcomes to be Measured

The primary outcome measured was the differences in the percentage of stunted infants (length-for-age <–2 *z* score) of children at 6, 12, 15, and 18 months. We also measured changes in mean length-for-age *z* scores from birth until 48 months.

### Secondary Outcomes to be Measured

We measured changes in the percentage of women EBF (breast milk and no other foods or milk-based liquids) their infants from 1 to 6 months. We also measured changes in the mean duration of any breastfeeding. We calculated the changes in the percentage of children at 6 and 9 months of age who received solid, semisolid, or soft foods; and the percentage of children consuming foods from 4 or more food groups at 9, 12, 15, and 18 months. We assessed bottle feeding (any liquid or semisolid food from a bottle with a nipple or teat) in infants at 7, 9, and 12 months. We measured the changes in mean cognitive function scores with the Ages and Stages Questionnaire (9 and 18 months) and Bayley tests (24 and 36 months).

### Measurements

#### Anthropometry

Trained research assistants collected the anthropometric measurements (weight and height) using established methods [36] and recorded these measurements on both the research instruments and an infant growth chart for the mother to keep. We standardized these measurements before and during the data collection. Anthropometry was collected soon after birth and every month up to 12 months, at 3-month intervals up to 18 months (15 and 18 months), and then at 24, 36, and 48 months. We used the 2006 WHO growth standards to construct anthropometric indices. We calculated the standard WHO-recommended indicators to assess stunting (height-for-age <–2 *z* score), wasting (weight-for-height <–2 *z* score), and being underweight (weight-for-age <–2 *z* score).

#### Infant Feeding Practices

We collected infant feeding data every month from birth to 6 months, and then at 3-month intervals between 6 and 18 months. We applied the standard Bangladesh Demographic Health Survey (DHS) questions about infant-feeding practices [37] and monitored these patterns at the 3 monthly data collection periods from birth until 18 months of age. These include questions about current breastfeeding status, current use of other liquids and solid foods, the timing of introduction of other liquids or solid foods, use of bottles for feeding, and information about who was providing advice about infant feeding among family and friends.

A senior research assistant monitored about 10% of the interviewer's scheduled visits. The supervisors checked questionnaires daily, and if the information was incomplete or not clear, they returned to the home on the next day to complete the data form. Senior research assistants verified the mother's reports of infant feeding practices through a 4-hour observation period in an unscheduled visit.

#### Dietary Intake

Trained interviewers collected 24-hour dietary recalls using standard methods starting at 6 months of age until 18 months. They recorded all the foods consumed 24 hours before the interview and measured the portion sizes in local utensils. They also recorded the recipes used to prepare foods, including the amounts of raw food used and the preparation methods. Research assistants analyzed and presented the nutrient intakes and food groups consumed. In a subsample of 10% of respondents, we took duplicate 24-hour recalls to assess within-person variability and to allow adjustment of the prevalence of low intake nutrients.

